#### Randomisation/Blinding

Participants will be stratified by Janssen or mRNA prime and randomised 1:1 fashion (DB versus PPB) using block randomisation.

Participants of this study will be blinded to their first study visit. At the time of the first study visit, they will be told whether they will be vaccinated in the DB or PPB. Blood will be drawn from all participants at the first study visit.

All participants randomized to the DB group will receive the same vaccine at the first study visit. All participants randomized to the PPB group will receive their vaccine 3 / 4 months later.

Vaccines will be prepared in the hospital pharmacy. Eight days after the boost, they will be asked to complete the side effects questionnaires for 7 days after the boost and blood will be drawn at all given time points.

## 4. STUDY POPULATION

### 4.1 Population (base)

Healthcare Workers (HCW) from 18 to 65 years old who were primed with one Janssen or two mRNA vaccines (Moderna or Pfizer). Individuals of all ethnicities will be recruited. Participants will be recruited from both the SWITCH-trial (Janssen primed HCWs) (1-3) and the Erasmus MC HCW-study (mRNA primed HCWs) (4, 5), as these participants are well characterized and documented in breakthrough infections and earlier responses to COVID-19 vaccinations. Participants may participate regardless of a previous SARS-CoV-2 infection(s). By randomizing over the different groups, we assume that the experienced infections are equally distributed over the groups. To assess whether this is truly the case, N-specific antibodies will be retrospectively measured in the pre-boost sample from all participants.

### 4.2 Inclusion criteria

1. Participant is willing and able to give written informed consent for participation in the trial.
2. Adult (male/female) between 18 and 65 years old
3. Sufficient level of the Dutch language to undertake all study requirements

### 4.3 Exclusion criteria

1. Adults younger than 18 or older than 65 years.
2. Adults primed with another vaccine than Janssen, Moderna or Pfizer.
3. History of allergic reactions likely to be exacerbated by any component of study vaccines (e.g. hypersensitivity to the active substance or any of the SmPC-listed ingredients of the Janssen/Pfizer/Moderna vaccine).
4. Adults that are pregnant.
5. Currently being treated for cancer.
6. Severe kidney failure or dialyses dependent.
7. Status after organ-, stem cell- or bone marrow transplantation.
8. Use of immunosuppressant's.
9. Epilepsy.
10. HIV.
11. Bleeding disorder (e.g. factor deficiency, coagulopathy or platelet disorder), or prior history of significant bleeding of bruising following IM injections of vene puncture.
12. Continuous use of anticoagulants, such as coumarins (e.g. acenocoumarol) or novel oral anticoagulants (i.e. apixaban, dabigatran etc).
13. Participants who are currently participating in another research trial.
14. All regular contra-indications of the vaccines will be applied.

### 4.4 Sample size calculation

The primary analysis of this study will consist of one comparison:

- The fold change (day of boost and day 28) in antibody response after an additional boost comparing Janssen and mRNA primed HCW in the direct boost arm.

The sample size calculation is based on the following assumptions:

- The sample size calculation takes the available data from the Erasmus MC HCW study.
- The log10 transformed difference in fold change 28 days after third vaccination (i.e., second booster after Janssen prime and first boost after mRNA prime) are *Janssen prime 1.344 (sd=0.451)*; *mRNA prime 1.151 (sd=0.449)*.
- The expected difference is estimated using the non-parametric Mann-Whitney U test (mean and standard deviations are used to estimated median and interquartile ranges). This procedure is readily available in G\*Power (version 3.1.9.7).

Based on the above assumptions, the study needs to recruit 91 patients in each arm to achieve 80% power at two-sided 5% significance level. We assume +/- 10% of study participants will be loss to follow-up. Therefore, the sample size in each arm will be 100 participants. The study contains two treatment arms and two groups resulting in a total sample size of 400 participants.

## 5. TREATMENT OF SUBJECTS

Vaccines against SARS-CoV-2 (wildtype) are standard of care in the Netherlands. This study will investigate the immune response and AEs after an additional boost in autumn 2022. Which vaccine will be used will depend on the advice of ZonMw and the RIVM. It could be the regular vaccine from Moderna or Pfizer, but also the new variant vaccine from Moderna. This depends on the speed at which the new vaccine is registered by the European Medicines Agency. If the HCW are not likely to participate in this study, they will not yet receive a booster vaccine and have to wait what the government policy will be.

### 5.1 Investigational product/treatment

All participants are vaccinated with the same vaccine. It is yet to be determined which vaccine will be used. The vaccine is given into the muscle of the upper arm. The vaccines will come directly from RIVM and are not part of the stock used for the national vaccination program. These vaccinations are reserved by RIVM for research purposes. All used vaccines are registered COVID-19 Vaccines.

### 5.2 Use of co-intervention (if applicable)

Not applicable

### 5.3 Escape medication (if applicable)

Not applicable

## 6. INVESTIGATIONAL PRODUCT

The vaccines that are used are officially registered by the EMA. It is yet to be determined which vaccine will be used. This will be advised by RIVM and OMT at the end of July.

| Vaccine | Registration date + Link SmPC                                                                                               |
|---------|-----------------------------------------------------------------------------------------------------------------------------|
| Pfizer  | 23/12/2021
Clean COVID-19 Vaccine SmPC-PL 21-DEC-2020 735AM EST-135PM CET (europa.eu)                    |
| Moderna | 06/01/2021
COVID-19 Vaccine Moderna, Common name-COVID-19 mRNA Vaccine (nucleoside modified) (europa.eu) |

### 6.1 Name and description of non-investigational product(s)

| Vaccine | Description                                                                                                                                                                                                                 |
|---------|-----------------------------------------------------------------------------------------------------------------------------------------------------------------------------------------------------------------------------|
| Pfizer  | Comirnaty contains a molecule called messenger RNA (mRNA) with instructions for producing a protein from SARS-CoV-2, the virus that causes COVID-19. Comirnaty does not contain the virus itself and cannot cause COVID-19. |
| Moderna | Moderna contains a molecule called messenger RNA (mRNA) with instructions for producing a protein from SARS-CoV-2, the virus that causes COVID-19. Comirnaty does not contain the virus itself and cannot cause COVID-19.   |

### 6.2 Summary of findings from non-clinical studies

Not applicable. The vaccine is registered.

### 6.3 Summary of findings from clinical studies

| Vaccine | Clinical findings                                                                                                                                                                                                                                                                           |
|---------|---------------------------------------------------------------------------------------------------------------------------------------------------------------------------------------------------------------------------------------------------------------------------------------------|
| Pfizer  | 43.548 patients
A two-dose regimen of BNT162b2 conferred 95% protection against Covid-19 in persons 16 years of age or older. Safety over a median of 2 months was similar to that of other viral vaccines. Safety and Efficacy of the BNT162b2 mRNA Covid-19 Vaccine - PubMed (nih.gov) |
| Moderna | 30.000 patients
Conclusions: The mRNA-1273 vaccine showed 94.1% efficacy at                                                                                                                                                                                                              |

|  |                                                                                                                                                                                                                                        |
|--|----------------------------------------------------------------------------------------------------------------------------------------------------------------------------------------------------------------------------------------|
|  | 
preventing Covid-19 illness, including severe disease. Aside from transient local and systemic reactions, no safety concerns were identified.
 
Efficacy and Safety of the mRNA-1273 SARS-CoV-2 Vaccine - PubMed (nih.gov)
 |
|--|----------------------------------------------------------------------------------------------------------------------------------------------------------------------------------------------------------------------------------------|

#### 6.4 Summary of known and potential risks and benefits

##### Potential risks from vaccine administration (Moderna / Pfizer).

Hypersensitivity to the active substance or to any of the excipients.

The most common side effects are usually mild or moderate and got better within a few days after vaccination. Local and systemic adverse reactions were reported more frequently after dose 2 than after dose 1.

Very common (>10%): pain and/or swelling at the injection site, lymphadenopathy (axillary on the same side as the injection site), headache, nausea, vomiting, muscle and joint pain, fatigue, chills, and fever.

Common (1-10%): (itchy) rash or redness at the injection side. Skin rash.

Uncommon (0.1-1%): itching at the injection side, insomnia, malaise, pain in extremities, tremor, sneezing, sore throat, hyperhidrosis, muscle weakness, backache, and asthenia.

Rare (0.01-0.1%): hypersensitivity (allergic reaction of skin and underlying tissue), urticaria. Acute peripheral facial paralysis or palsy (in reports seen from day 22 to day 32 after the 2nd dose with Moderna and from day 3 to 48 after vaccination with Pfizer).

Facial swelling reported in individuals who have had facial dermal fillers in the past (Moderna).

Very rare (<0.01%): thrombosis in combination with thrombocytopenia; includes venous thrombosis such as cerebral venous sinus thrombosis, splanchnic venous thrombosis and arterial thrombosis.

Furthermore, anaphylaxis and hypersensitivity have been reported.

As for all vaccines, the vaccines will be given under close supervision with appropriate medical treatment available.

##### Potential benefits

These vaccines offer a high level of protection against COVID-19 which is a critical need in the current pandemic (see table for efficacy rates). Most side effects are mild to moderate in severity and are gone within a few days. The European Medicines Agency therefore decided that these vaccine benefits are greater than its risks and that they can be authorized for use in the EU. All vaccines have been granted a conditional marketing authorization. This means that there is more evidence to come about the vaccine, which the company is required to provide. The European Medicines Agency will review any new information that becomes available and this overview will be updated as necessary. However, the evidence is overwhelming that these vaccines at least prevent hospitalizations from COVID.

| Vaccine | Efficacy (depended on variant) |
|---------|--------------------------------|
| Pfizer  | up to 95%                      |
| Moderna | up to 95%                      |

### 6.5 Description and justification of route of administration and dosage

All vaccines will be administered according to their respectively SmPC registration.

Also the dosage will be administered according to the SmPC.

All vaccines are given into the muscle of the upper arm.

### 6.6 Dosages, dosage modifications and method of administration

| Vaccine | Dosage                                  |
|---------|-----------------------------------------|
| Pfizer  | 0.3 ml IM after dilution with NaCl 0.9% |
| Moderna | 0.25 ml IM                              |

### 6.7 Preparation and labelling of Non Investigational Medicinal Product

| Vaccine | Preparation                                                                                                                                                                                                                                                                             |
|---------|-----------------------------------------------------------------------------------------------------------------------------------------------------------------------------------------------------------------------------------------------------------------------------------------|
| Pfizer  | The thawed vaccine must be diluted in its original vial with 1.8 mL sodium chloride 9 mg/mL (0.9%) solution for injection, using a 21 gauge or narrower needle and aseptic techniques.
Gently invert the diluted dispersion 10 times. Do not shake.
Withdraw 0.3 mL of Comirnaty. |
| Moderna | Withdraw 0.25 mL of Moderna.                                                                                                                                                                                                                                                            |

### 6.8 Drug accountability

The vaccines will be supplied by the RIVM after approval by ZonMw and Ministry of Health, wellbeing and sports (VWS). It is important to state that the vaccines for this study will NOT be retrieved from a stock reserved for patients or other persons.

As is usual in routine care at this moment, the batch numbers will be recorded for each patients ensuring its traceability. Vaccines will be shipped to the pharmacy. A drug accountability form will be used to record IMP dispensing.

## **7. NON-INVESTIGATIONAL PRODUCT**

### **7.1 Name and description of non-investigational product(s)**

Not applicable

### **7.2 Summary of findings from non-clinical studies**

Not applicable

### **7.3 Summary of findings from clinical studies**

Not applicable

### **7.4 Summary of known and potential risks and benefits**

Not applicable

### **7.5 Description and justification of route of administration and dosage**

Not applicable

### **7.6 Dosages, dosage modifications and method of administration**

Not applicable

### **7.7 Preparation and labelling of Non Investigational Medicinal Product**

Not applicable

### **7.8 Drug accountability**

Not applicable

This paragraph is not applicable. Only vaccines will be used described in paragraph 6.

## 8. METHODS

### 8.1 Study parameters/endpoints

#### 8.1.1 Main study parameter/endpoint

The primary endpoint is to determine the fold change in antibody level at day of boost and 28 days after an additional COVID-19 booster vaccination in the direct boost group, comparing Janssen with mRNA-primed HCW.

To specifically answer the key objective, we have defined two questions with the following outcome parameters:

1) *Is there an increase in antibody levels between day of boost and 28 days after boosting HCW that were initially primed with either the Janssen or an mRNA-based vaccine?*

**Outcome:** Level and fold change of antibodies determined by a quantitative IgG assay comparing the Janssen primed and mRNA-based primed HCW.

2) *Does booster vaccination lead to a rapid secondary recall response, indicative of immunological memory?*

**Outcome:** Level and fold change of antibodies and T-cell responses determined by a quantitative IgG assay and whole blood IFN $\gamma$  release assay, respectively, comparing day 7 and 28 post-boost.

Depending on whether it is possible to conduct this study with a bivalent vaccine, we will add an Omicron BA.1 IgG test to the arsenal of analyses.

#### 8.1.2 Secondary study parameters/endpoints

##### Secondary endpoints:

In addition to the primary endpoints defined above, this study will address the following secondary objectives:

1. *What is the difference in booster immunogenicity comparing a direct boost with a postponed boost?*

**Outcome:** Level of antibodies and T-cell responses 7 and 28 days post boost in DB versus PPB group.

2. *What is the breadth of the immune responses after booster vaccination?*

**Outcome:** PRNT against relevant variants in a random selection of study participants.

3. *What is the predictive value of immune responses on day 7 post boost?*

**Outcome:** Relationship between antibodies and T-cell responses on day 7 and 28 post boost.

4. *What is the difference in reactogenicity 7 days after boost comparing the Janssen and mRNA primed HCW?*

**Outcome:** Adverse events (AE) first 7 days after an additional boost between Janssen and mRNA primed HCW.

5. *Initial examination of breakthrough infections before and during study period*

**Outcome:** Database of breakthrough infections in included participants based on positive PCR, self-reported positive lateral flow test, or detection of N-specific antibodies.

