#### Study groups

This study will consist of 2 cohorts; SWITCH study (Janssen prime - from four university hospitals; Amsterdam UMC, Erasmus MC, Leiden UMC, and UMC Groningen) and HCW study (mRNA prime from Erasmus MC) (n=200 per cohort).

| Group       | Intervention* | Number of participants | Neutralization (3 variants) |
|-------------|---------------|------------------------|-----------------------------|
| DB mRNA     | Boost         | 100                    | 15                          |
| DB Janssen  | Boost         | 100                    | 15                          |
| PPB mRNA    | Boost         | 100                    | 15                          |
| PPB Janssen | Boost         | 100                    | 15                          |

*\*Which vaccine will be administered as intervention remains to be determined, based on availability.*

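### The PRNT (breadth) comparison rests on 15 participants per group and is planned unadjusted, although N-antibody status is measured in everyone and could recover most of the precision lost to chance imbalance in prior infection

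*Protocol*

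**What the plan says.** The Study groups table in Section 3 gives the subset size group by group, for example "DB mRNA | Boost | 100 | 15", the last column being the number tested for neutralisation of three variants. The other three groups have the same figure, so 60 of 400 participants are tested. No calculation supports the 15.

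Secondary objective 2 describes the outcome as "PRNT against relevant variants in a random selection of study participants" (Summary, Section 2, Section 8.1.2 and Section 10.2). None of these places names a stratifying factor.

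Section 4.1 admits participants whether or not they have been infected before, and says: "By randomizing over the different groups, we assume that the experienced infections are equally distributed over the groups". To check this, "N-specific antibodies will be retrospectively measured in the pre-boost sample from all participants".

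Section 10 says that secondary outcomes are analysed with tests of the kind used for baseline characteristics: a t-test or Mann-Whitney test for continuous variables, and a chi-square or Fisher test for categorical ones. No covariate is mentioned. The significance cut-off is p below 0.01.

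**The concern.** The protocol treats prior infection as something that could differ between groups, and measures it in all participants. In the smallest sample of the trial it then states an analysis that makes no use of the measurement. The assumption of balance in Section 4.1 is made for the randomised groups of 100. It says little about subsets of 15, where chance differences are much larger. If prior infection shifts neutralising titres, that variation enters the unadjusted comparison as noise. With 15 per group and a 0.01 cut-off there is little precision to spare.

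**Working it through.** **The plan's own figure.** There is no precision figure for PRNT to reproduce. The primary sample size is the only source in the protocol for a log10 antibody SD, so it was checked first. The difference is 1.344 − 1.151 = 0.193. The pooled SD is √((0.451² + 0.449²)/2) = 0.450, so d = 0.193/0.450 = 0.429. A t-test needs 87 per arm. A Mann-Whitney test with relative efficiency 3/π needs 91 (power 80.3%). This agrees with Section 4.4: "the study needs to recruit 91 patients in each arm to achieve 80% power at two-sided 5% significance level".

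**Inputs for the PRNT check**
- From the protocol: 15 drawn from 100 in each group.
- Assumed: share N-positive p = 0.3 to 0.7, equal in the two groups of 100 being compared.
- Assumed: N status shifts log10 PRNT titre by δ = 0.2 to 0.6.
- Assumed: within-stratum SD of 0.45, borrowed from the IgG fold change because no PRNT SD is given.

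**Step 1: imbalance.** Drawing 15 of 100 without replacement is hypergeometric. The SD of the between-group difference in N-positive share is √(2p(1−p)/15 × 85/99), which is 0.169 at p = 0.5 and 0.155 at p = 0.3 or 0.7.

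| N-positive share | gap ≥ 3 of 15 | gap ≥ 4 | gap ≥ 5 |
|---|---|---|---|
| 30% or 70% | 28% | 13% | 5% |
| 50% | 32% | 17% | 7% |

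**Step 2: standard error of the difference in mean log10 titre between two groups**
- Stratified draw: √(2 × 0.45²/15) = √0.027 = 0.1643.
- Random draw, unadjusted: √(2 × (0.45² + p(1−p)δ² × 85/99)/15).
- Random draw with N status as a factor: simulated, 12,000 runs per setting.

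| share | δ | unadjusted SE | excess over 0.1643 | adjusted SE |
|---|---|---|---|---|
| 30% or 70% | 0.2 | 0.1672 | 1.8% | 0.1662 / 0.1656 |
| 30% or 70% | 0.3 | 0.1708 | 4.0% | 0.1659 / 0.1663 |
| 30% or 70% | 0.4 | 0.1756 | 6.9% | 0.1662 / 0.1676 |
| 30% or 70% | 0.6 | 0.1888 | 14.9% | 0.1681 / 0.1687 |
| 50% | 0.2 | 0.1678 | 2.1% | 0.1672 |
| 50% | 0.3 | 0.1720 | 4.7% | 0.1655 |
| 50% | 0.4 | 0.1777 | 8.2% | 0.1667 |
| 50% | 0.6 | 0.1931 | 17.5% | 0.1666 |

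In the 30% or 70% rows the two adjusted values are for 30% and 70% in that order.

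**Step 3: what each remedy contributes.** In the most favourable setting (50%, δ = 0.6), adjustment takes the SE from 0.1931 to 0.1666, and stratified selection would take it to 0.1643. Adjustment therefore recovers (0.1931 − 0.1666)/(0.1931 − 0.1643) = 0.0265/0.0288 = 92% of the loss. Over all settings the stratified SE is 0.7% to 2.6% below the adjusted one, mostly 1–2%. At δ = 0.2 the whole loss is only about 2%, so neither remedy matters much.

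**The case against.** **The draw may already be stratified.** A reader might infer that the protocol commits to a simple random draw that ignores N status. It does not: the wording allows a draw stratified within group, and such detail may sit in a statistical analysis plan that is not shown. This stands for the selection rule. It stands less well for the analysis, because Section 10 does state the tests for secondary outcomes, and they are unadjusted.

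**Stratified selection is not free, nor the main remedy.** A reader might infer that it would make 15 participants worth up to about 21 at no cost (15 × 1.175² = 20.7). That compares it only with an unadjusted analysis. Once N status is in the model, the further gain is about 1–2% in SE. N antibodies are also to be measured retrospectively, so the draw would have to wait for the results. If the PRNT subset is the detailed immunological assessment group of Section 8.3, whose extra tubes start on day 0, that may be impossible. The protocol does not say whether the two are the same.

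**Objective 2 names no group contrast.** Unlike objectives 1 and 4, it asks only about breadth after boosting. That can be read across variants within a person, where a shift common to all variants cancels. This stands: the figures above apply to comparisons of mean titre between groups, which the group-wise quota and Section 10 suggest but objective 2 does not spell out.

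**An equal N-positive split in all four groups could distort the subset.** This stands too. Prime is not randomised, and the two primes come from different cohorts. If infection truly differs between them, a forced common split no longer describes either cohort.

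**Conclusion.** The point holds as a missed efficiency on a secondary endpoint. With 30–70% N-positive, two groups of 15 differ by four or more N-positive participants in 13–17% of draws. The unadjusted SE is then about 2% to just over 17% larger than it need be, for an assumed shift of 0.2–0.6 log10 and SD 0.45. The prevalence and the shift are not in the protocol, and the SD is borrowed from another assay measure, so the size is indicative only.

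A reader might go further and infer that the PRNT results would be biased or invalid. The documents do not support that: a random selection represents the group from which it is drawn. Nothing here is a contradiction or an error, and the primary comparison is not affected.

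**What to change.** In Section 10, state that PRNT titres are compared between groups on the log10 scale in a linear model with pre-boost N-antibody status as a factor. Name the sample used. For the postponed group the protocol does not say whether pre-boost means day 0 or the boost visit at day 90 or 112. The day-0 sample exists for everyone and precedes any effect of postponement. The cost is one degree of freedom (27 instead of 28 for two groups of 15) and no extra assays, since N antibodies are already planned for all.

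Optionally, if the day-0 N assay can be run before the PRNT list is drawn, stratify the draw on N status within each group. The direct and postponed groups of the same prime may share one split, because they are randomised. Do not impose one split across the Janssen and mRNA cohorts without reweighting. The cost is a change in the order of laboratory work, for about 1–2% in SE. Either way, say in Section 8.1.2 how the 15 are drawn and whether they are the detailed immunological assessment group.
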